# 8. Study Procedure

Before the study begins, the patient must read and sign a current informed consent form approved by the Ethics Committee (EC). All study steps have to be carried out within time frames designated in the study plan.

## 8.1 Screening Period

Unless otherwise specified, the following steps have to be completed in 28 days before starting the treatment with the study drug:

- Case history and demographic data acquisition, and recording (by the investigators) identity card, correspondence address, and phone number of every patient, though such information will not be recorded in a CRF;
- Detailed inquiry of case history, and detailed comprehensive physical examination: ECOG score, height, body weight, vital signs, and checkup of various organs;
- Routine blood test, and routine urinalysis;
- Blood chemistry (myocardial zymogram, cardiac troponin, GGT, ALT, AST, ALP, TP, ALB, ALB/GLO, TBIL, IBIL, DBIL, BUN, Cr, Glu, K^+^, Na^+^, Cl^－^, LDH, TC, TG, HDL-C, and LDL-C);
- Blood coagulation tests (INR, APTT, and PT);
- HER2 protein expression and gene amplification assays: immunohistochemistry (ICH), and fluorescence in situ hybridization (FISH);
- Tumor markers (specific test items will be determined by the investigators depending on the tumor type);
- Virology test (HIV, five HBV tests, and HCV);
- Electrocardiographic examination for 3 times at intervals of 5 minutes, particularly observing QT, QTc and P-R intervals (within 7 days before the initiation of the trial);
- Echocardiographic examination to observe LVEF (within 28 days before the initiation of the trial);
- CT or MRI scans of the chest, abdomen, pelvis, brain and other relevant lesions (within 28 days before the initiation of the trial);
- Urine HCG tests for female patients of childbearing age to exclude pregnant subjects;
- Assessment of current concomitant medications and treatments;
- Assessment of current symptoms.

Written informed consent forms must be obtained before any of the study-related medical procedures. CT/MRI scan results obtained prior to the signing of informed consent forms can be used for the tumor assessments during screening (examination must be made within 28 days before the initiation of the trial).

## 8.2 Trial Period

The following procedures should be completed in accordance with the trial schedule:

- Perform physical examination and ECOG evaluation for every cycle;
- Examine patients for vital signs every medication cycle, measure body weight before each administration, and monitor vital signs at the point of pharmacokinetic blood collection during the initial administration;
- Examine the following items before each administration: routine blood test, routine urinalysis, blood chemistry (Troponin, GGT, ALT, AST, ALP, TP, ALB, ALB/GLO, TBIL, IBIL,DBIL, BUN, Cr, Glu, K+, Na+, Cl－, LDH, TC, TG, HDL-C, and LDL-C);
- Test blood coagulation function (INR, APTT and PT) once every treatment cycle;
- Tumor markers (specific test items will be determined by the investigators depending on the tumor type);
- Perform ECG examination 3 times at intervals of 5 minutes before each administration, monitor ECG during medication, and perform ECG examination 3 times at intervals of 5 minutes within 1-2 h after administration. If the subject experiences precordial chest pain, palpitations or other symptoms, or has an abnormal ECG, CK-MB test and echocardiography may be added;
- Perform tumor imaging examination, including CT or MRI scans of the chest, abdomen, pelvis, brain and other related lesions:
  - wherein, for subjects rated as CR or PR at the initial evaluation, their efficacy should be verified 4 weeks later, and tumor assessment after verification should follow the previously established examination time points;
  - when the treatment ends or subject withdraws (if no tumor assessment has been performed within the preceding 4 weeks).
- Record adverse events: from Day 1 of treatment to at least 21 days after the last dosing, or until all severe or drug-related toxic reactions are safely eliminated or returned to Grade 1 as specified in NCI CTCAE 4.0. In addition, observe and record clinical manifestations during medication;
- Record concomitant medications or treatments: from 4 weeks before the initiation of the study to at least 21 days after the last dosing.

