**1.5 Preliminary Study Results**

As of July 1, 2017, a total of 25 valid subjects have been enrolled in the study. Dose escalation has reached 2.5 mg/kg, with DLT of Grade 4 neutropenia occurring in 2 cases at the dose of 2.5 mg/kg. Drug-related adverse events (≥5%) included leukopenia (14%), neutropenia (9%), decreased hemoglobin (7%) and numbness (6%). Adverse events that led to changes in medication (including dose reduction, dosing suspension and medication termination) were leukopenia, neutropenia and numbness of hands and feet. All symptoms were resolved after dose discontinuation or symptomatic treatment.

As of July 1, 2017, efficacy evaluation has been conducted on 19 subjects, among which 3 were evaluated as partial response (PR), 8 were stable disease (SD), and 8 were progressive disease (PD). The duration time for administration is up to 238 days.

Pharmacokinetic study showed that half-lives of RC48-ADC in the groups of 1.0 mg/kg, 2.0mg/kg and 2.5mg/kg were 16.2±9.5 h, 34.4±13.7 h and 49.0±27.4 h, respectively. Exposure level AUC_0-∞_ increased with dose. No anti-drug antibody was detected so far.

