**On July 4, 2017, the investigators and sponsor decided to modify the DLT definition based on the current study results:**

**DLT** refers to the following toxic reactions observed in the DLT evaluation window (observation period of Day 1-21 after the first dose) that are considered related to RC48-ADC treatment by the investigators or sponsor, wherein the grading is based on the 5-level system of the CTCAE v4.0:

- Grade 4 neutropenia lasting more than 3 days after symptomatic treatment; or grade 4 neutropenia recurring after recovery to a normal level through symptomatic treatment.
- Neutropenic fever (defined as absolute neutrophil count ^[^ANC] < 1000/mm3 accompanied by a fever higher than 38.3 °C or a fever above 38 °C that persists for more than 1 h).
- Grade 3 neutropenia with confirmed infections.
- Grade 3 thrombocytopenia with bleeding tendency.
- Grade 4 thrombocytopenia.
- Non-hematologic toxicity of Grade 3 or higher after supportive care. Except for nausea, vomiting and hair loss.
- Renal toxicity ≥ Grade 3.
- Neurological toxicities ≥ Level 2 that persist until the next administration.
- Cardiac toxicity ≥ Grade 2.
- Hepatic transaminases reach grade 2 at baseline, with a level ≥10×ULN.

If DLT appears in the subjects, treatment of RC48-ADC should be discontinued first, and adverse reactions should be dealt with actively until the toxicity returns to ≤ Grade 1. Thereafter, medication should proceed at a decreased dose level (specific doses will be determined by the investigators).

**Maximum Tolerated Dose (MTD)**: The lower dosage next to a dose with which DLT occurs in 2 or more out of 6 patients during the DLT evaluation window.

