**Blood Collection for PK During Dose-Escalation Trial:**

Blood collection time points for Q2W administration:

The blood collection points for the first dose (11 blood collection points): before administration (0 h), 0.25 h, at the end of infusion, 1.5 h, 12 h, 24 h, 48 h, 72 h, 120 h, 168 h and 240 h.

For the second dose (1 blood collection point): before administration (336 h).

For the third dose (1 blood collection point): before administration (672 h).

For the fourth dose (12 blood collection points): before administration (1008 h), 0.25 h (1008.25 h), at the end of infusion, 1.5 h (1009.5 h), 12 h (1020 h), 24 h (1032 h), 48 h (1056 h), 72 h (1080 h), 120 h (1128 h), 168 h (1176 h), 240 h (1248 h) and 336 h (1344 h).

Blood samples are collected at these 25 time points to detect serum ADC, TAb and free MMAE, with a collection volume of 2 mL each time.

Blood collection points for immunogenicity (ADA) assays: Serum anti-ADC antibodies are detected before the first, second, third and fourth doses, and 336 hours after the fourth dose (5 collection points), with 1 mL of blood volume for each sample.

Blood collection time points for Q3W administration:

The blood collection points for the first dose (11 blood collection points): before administration (0 h), 0.25 h, at the end of infusion, 1.5 h, 12 h, 24 h, 48 h, 72 h, 120 h, 168 h and 240 h.

For the second dose (1 blood collection point): before administration (504 h).

For the third dose (12 blood collection points): before administration (1008 h), 0.25 h (1008.25 h), at the end of infusion, 1.5 h (1009.5 h), 12 h (1020 h), 24 h (1032 h), 48 h (1056 h), 72 h (1080 h), 120 h (1128 h), 168 h (1176 h), 336 h (1344 h) and 504 h (1512 h).

Blood samples are collected at these 24 time points to detect serum ADC, TAb and free MMAE, with a collection volume of 2 mL each time.

Blood collection points for immunogenicity (ADA) assays: Serum anti-ADC antibodies were detected before the first, second and third doses, and 504 h after the third dose (4 collection points), with 1 mL of blood volume for each sample.

Blood collection time points for QW administration:

The blood collection points for the first dose (9 blood collection points): before administration (0 h), 0.25 h, at the end of infusion, 1.5 h, 12 h, 24 h, 48 h, 72 h and 120 h.

For the second dose (1 blood collection point): before administration (168 h).

For the third dose (1 blood collection point): before administration (336 h).

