# Appendix 2. Trial Flow Chart of Dose Escalation Phase - Q2W Administration

| Visit Time Points | Screening | Cycle 1-2 | | Extended Trial | Conclusion/Withdrawal |
| --- | --- | --- | --- | --- | --- |
|  | -28 | D 1 (±1) of Cycle 1 | D 1 (±1) of Cycle 2 | D 1 (±2) of Cycle 3-n |  |
| Informed Consent | √ |  |  |  |  |
| **General Medical History Collection** |  |  |  |  |  |
| Inclusion/Exclusion Review | √ |  |  |  |  |
| Filling of General Information | √ |  |  |  |  |
| Past medical history | √ |  |  |  |  |
| Combined diseases and treatment history | √ |  |  |  |  |
| **ECOG** Scale | √ | √ |  |  |  |
| Virology test | √ |  |  |  |  |
| **Safety Examination** |  |  |  |  |  |
| Vital signs | √ | √ | √ | √ | √ |
| Routine blood test | √ | **√△** | **√** | √ | √ |
| Routine Urinalysis | √ | **√△** | **√** | √ | √ |
| Blood chemistry | √ | **√△** | **√** | √ | √ |
| Blood coagulation test | √ | **√△** | **√** |  |  |
| Pharmacokinetics and Immunogenicity |  | See Item 6 in the Clinical Trial Protocol | |  |  |
| Electrocardiography | √ | √※ | √※ | √☆ | √ |
| Urine pregnancy test | √ |  |  |  | √ |
| Echocardiography | √ | √★ | | | √ |
| HER2 Detection | √ |  | | |  |
| Tumor Marker ▲ | √ | **√△** |  | √ |  |
| Imaging Examination# | √ | Once every 2 cycles | | |  |
| Efficacy Evaluation |  | Once every 2 cycles | | |  |
| Record the adverse events |  | √ | √ | √ | √ |
| Record concomitant medication | √ | √ | √ | √ | √ |

△ If the interval between the 1st dose and the screening period should be no more than 7 days, no reexamination is required.

※ Perform ECG examination 3 times at intervals of 5 minutes before each dose. Monitor ECG during medication. Perform ECG examination 3 times at intervals of 5 minutes within 1-2 hours after administration.

★ If the subject experiences precordial chest pain, palpitations or other symptoms, or has an abnormal ECG, CK-MB test and echocardiography may be added.

▲ Specific test items will be determined by the investigators depending on the tumor type.

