# At baseline, all patients with solid tumors must undergo CT/MRI scans of the chest, abdomen and pelvis according to the RECIST v1.1. For osteopathy patients, confirmatory bone scan shall be carried out at the time of baseline. Tumor assessment will be performed by using CT/MRI/radiography. For subjects rated as CR or PR at the initial evaluation, their efficacy should be verified 4 weeks later. 1 evaluation should be performed every 2 cycles.

☆ ECG is required before each dose.

Note: Each treatment cycle includes 2 doses, and the efficacy should be evaluated every 2 treatment cycles.

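### The scheduled blood counts do not ensure that silent Grade 4 cytopenias are detected, or the duration of Grade 4 neutropenia measured, in the 21-day DLT window

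*Protocol*

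**What the plan says.** The DLT window in section 3 is the "observation period of Day 1-21 after the first dose". For the dose-escalation phase, section 8.2 has: "Examine the following items before each administration: routine blood test, routine urinalysis, blood chemistry". It sets no count between doses.

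The Q2W flow chart (Appendix 2) places its treatment-phase blood tests at "D 1 (±1) of Cycle 1 | D 1 (±1) of Cycle 2", and its note reads: "Note: Each treatment cycle includes 2 doses, and the efficacy should be evaluated every 2 treatment cycles". The QW flow chart (Appendix 5) has the same columns and the same note. In both charts the Cycle 1 count may be omitted if screening was no more than 7 days earlier.

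Until July 4, 2017 any Grade 4 neutropenia was a DLT. The amended definition (section 3, repeated in section 18) requires "Grade 4 neutropenia lasting more than 3 days after symptomatic treatment", or recurrence of Grade 4 after recovery under treatment. Section 10.2 allows G-CSF once Grade 4 neutropenia is present but not as prevention. No section says how soon a Grade 4 count must be repeated.

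Section 1.5 reports the experience before the amendment: dose escalation had reached 2.5 mg/kg, "with DLT of Grade 4 neutropenia occurring in 2 cases at the dose of 2.5 mg/kg".

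**The concern.** Neutropenia is the only DLT reported so far, and the amended criterion for it needs serial counts: one to find the episode, and more to show that it outlasted 3 days after treatment or came back after recovery. Counts 7 to 14 days apart are poorly suited to either purpose. The clock also starts at treatment, so an asymptomatic episode that is never counted is never treated and cannot meet the criterion.

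The MTD is a primary objective and is set by 3+3 counting of DLTs. Q2W escalation resumes from 2.5 mg/kg, the dose at which the earlier criterion had produced two DLTs, with planned steps up to 4.0 mg/kg. The amended criterion now carries that decision. A DLT that goes unrecorded is scored as no DLT.

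**Working it through.** The protocol states no detection rate or operating characteristic here, so there is no figure to reproduce.

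**Step 1. Counts inside the window.** Day = 1 + hours/24. For Q2W, section 6 has "For the second dose (1 blood collection point): before administration (336 h"), which is Day 15; dose 3 at 672 h is Day 29. For QW, doses 2, 3 and 4 at 168, 336 and 504 h are Days 8, 15 and 22. With two doses per cycle, Day 1 of Cycle 2 is Day 29 under Q2W and Day 15 under QW.

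| Schedule | Post-dose counts in Day 1-21, section 8.2 | Same, flow chart |
| --- | --- | --- |
| Q2W | Day 15 | none (next is Day 29) |
| QW | Days 8 and 15 | Day 15 |

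Section 8.2 and the flow charts therefore disagree for both schedules.

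**Step 2. Chance that a scheduled count falls in a Grade 4 episode.** Assumption, not a protocol figure: an episode of D days lies wholly within Days 2-21 with onset uniform on 2 to 21-D, a range of 19-D days. A count on day x catches it if onset lies between x-D and x.

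- Q2W, section 8.2 (Day 15): D=4, 4/15 = 0.27; D=5, 5/14 = 0.36; D=7, 6/12 = 0.50; D=10, 6/9 = 0.67.
- QW, section 8.2 (Days 8 and 15): D=4, 8/15 = 0.53; D=5, 10/14 = 0.71; D=7 or 10, 1.00.
- Q2W by Appendix 2: 0 at every length.

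These figures show whether any Grade 4 count is seen, not whether the duration criterion is met.

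**Step 3. Chance that duration shows from the schedule alone.** This needs two in-window counts in the same episode. Under Q2W there is only one post-dose count, so the chance is 0 at every length. Under QW, Days 8 and 15 are 7 days apart: 0 up to D=7, 1/11 = 0.09 at D=8, and 3/9 = 0.33 at D=10.

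**Step 4. Effect on 3+3.** Escalation follows 0 DLTs in 3, or 1 in 3 and then 0 in 3 more: P = (1-p)^3 + 3p(1-p)^5, which falls as p rises. If only a share s of DLTs is recorded, p becomes s×p, so P can only rise.

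- p=0.40, s=1: 0.216 + 1.2×0.0778 = 0.31. With s=0.5 (p=0.20): 0.512 + 0.6×0.3277 = 0.71.
- p=0.33: 0.43 with s=1, 0.61 with s=0.75, 0.78 with s=0.5.

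Both p and s are assumptions. Halving the whole rate is a worst case, because it treats every kind of DLT as equally likely to be missed.

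**The case against.** The strongest reply is that scheduled counts are not the only counts. Section 9 keeps subjects in hospital throughout PK collection and requires laboratory abnormalities to be recorded with time of occurrence and duration. Section 11.1 requires follow-up of abnormal results. Since the amended criterion runs from treatment, its clock usually starts after the episode has been found, when that follow-up applies. Two Grade 4 neutropenia DLTs were in fact recorded. Neutropenic fever, neutropenia with confirmed infection and thrombocytopenia with bleeding would show themselves clinically, and the cardiac, neurological and other non-hematologic criteria do not depend on interim counts.

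Much of this stands. A reader might infer that hematologic DLTs cannot be ascertained at all; the protocol does not support that. A reader might also take 0.31 to 0.71 as the expected effect; it is not, because it assumes that half of all DLTs go unseen.

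What remains is that none of these provisions fixes a count. The hospital stay carries no count schedule, follow-up of an abnormal result presupposes that a count was taken, and section 11.1 gives no interval. The PK samples are assayed for ADC, total antibody and MMAE, not blood cells. Under Q2W no blood sample is scheduled between Day 15 and Day 29. The two recorded cases arose when a single Grade 4 count sufficed, so they do not show that duration is measurable.

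**Conclusion.** The point holds for asymptomatic Grade 4 cytopenias and for the duration and recurrence of Grade 4 neutropenia, most clearly under Q2W. Followed exactly, the Q2W schedule has at most one post-dose count in the window and cannot show either limb of the amended criterion. The conflict between section 8.2 and Appendices 2 and 5 stands without any assumption.

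The direction of any error is certain: missed DLTs favor escalation, so the MTD is at risk of being set too high. A reader might infer that it is biased upward as a matter of fact. That is not shown, because the size depends on unscheduled testing, which the protocol does not quantify. The detection figures rest on the uniform-onset assumption and the 3+3 figures on assumed p and s.

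A reader might also infer that unequal detection makes the Q2W and QW MTDs non-comparable. No section plans that comparison, and the window already holds two Q2W doses against three QW doses by design.

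**What to change.** Reconcile section 8.2 with Appendices 2 and 5 on when blood tests are done, and then:

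- **Q2W:** add a routine blood count to the existing dose-1 PK draws at 72 h and later ("48 h, 72 h, 120 h, 168 h and 240 h" lists them, 48 h not being needed), that is Days 4, 6, 8 and 11. Keep the pre-dose-2 count at 336 h (Day 15).
- **QW:** add counts at the existing 72 and 120 h draws. The dose-1 PK series ends there, and 168 h is already pre-dose 2. Keep the pre-dose counts at 168 and 336 h, and add between-dose counts after doses 2 and 3.
- **Both:** add one count near Day 21, which is a new draw.
- **After any Grade 4 count:** repeat at a stated interval short enough to establish more than 3 days and to detect recurrence.
- **Evaluability:** a subject without a DLT who lacks these counts is not DLT-evaluable and is replaced. A subject with any DLT always counts, so that missing later counts cannot remove toxicity from the denominator.

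Under the assumption in Step 2, Q2W counts on Days 4, 6, 8, 11, 15 and 21 would catch 13/15 = 0.87 of 4-day episodes, 13/14 = 0.93 of 5-day episodes and all 7-day episodes. The remaining gap is Days 15 to 21.

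The cost is amendment wording, a few routine counts, one or more extra venepunctures (mainly under QW and at Day 21), and slightly more blood volume and laboratory expense. No dose or treatment rule changes.

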## 8.3 Extended Trial

Patients evaluated as CR, PR and SD in the first efficacy evaluation during dose escalation phase can enter the extended trial on a voluntary basis, provided that investigators estimate that continuous medication would be beneficial to the patient. A time frame of ±3 days is allowed for all tests (except imaging examination) for each visit. An extended trial should include the following tests:

- ECOG evaluation;
- Body weight measurement, physical examination and vital sign examination for 1 time;
- Examine the following items before each administration: routine blood test, routine urinalysis, blood chemistry (Troponin, GGT, ALT, AST, ALP, TP, ALB, ALB/GLO, TBIL, IBIL,DBIL, BUN, Cr, Glu, K+, Na+, Cl－, LDH, TC, TG, HDL-C, and LDL-C);

On July 4, 2017, the investigators and sponsor decided to discontinue the original dose-escalation study starting with 2.0 mg/kg Q3W. Instead, a dose-escalation study with an initial dose of 1.25 mg/kg QW was added. Subjects participating in the extended trial should undergo routine blood test, routine urinalysis, blood biochemical examination before the initial administration of each treatment cycle;

- Tumor markers (specific test items will be determined by the investigators depending on the tumor type);
- ECG examination before each administration; if the subject experiences precordial chest pain, palpitations or other symptoms, or has an abnormal ECG, CK-MB test and echocardiography may be added;

On July 4, 2017, the investigators and sponsor decided to discontinue the original dose-escalation study starting with 2.0 mg/kg Q3W. Instead, a dose-escalation study with an initial dose of 1.25 mg/kg QW was added. Subjects participating in the extended trial should undergo ECG examination before the initial administration of each treatment cycle. If the subject experiences precordial chest pain, palpitations or other symptoms, or has an abnormal ECG, CK-MB test and echocardiography may be added;

- Tumor imaging examination, including CT or MRI scans of the chest, abdomen, pelvis, brain and other related lesions. For subjects rated as CR or PR at the initial evaluation, their efficacy should be verified 4 weeks later. A time frame of ±7 days is allowed. Specific evaluation time points are as follows:
  - once every 2 treatment cycles;
  - when the treatment ends or subject withdraws.

A 3 mL fasting blood sample is collected before each administration on the day of tumor evaluation (on the day of imaging examination) during the 3rd-8th treatment cycles. Samples are used for the detection of serum TAb, ADC, plasma free MMAE concentration, as well as serum anti-ADC antibodies (ADA, anti-RC48-ADC antibodies) to investigate PK/PD correlation and evaluate the relationship between trough concentration and efficacy.

- Record adverse events: until at least 21 days after the last dosing;
- Record concomitant medications or treatments: until at least 21 days after the last dosing.

## 8.4 Extended Trial

On July 4, 2017, the investigators and sponsor decided to let 3-5 study sites participate in the extended trial phase based on the current study results. At least 10 patients with HER2 ICH 2+/FISH- and at least 20 patients with HER ICH 2+/FISH+ or ICH 3+ with advanced solid tumors (gastric cancer is preferable) are enrolled and administered at 2.0 mg/kg Q2W until disease progression or intolerable adverse reactions. A treatment cycle consists of 2 doses. Efficacy is evaluated once every 2 cycles. Specific items are shown in Appendix 4 Flow Chart of Extended Trial.

